#### Secondary outcome measurements

Secondary outcomes will include intensity of LBP measured with VAS, and will likewise try to reduce error with the following question: “Please rate the pain intensity you feel during daily activities.”

LBP and sciatic pain intensity will also be assessed with NRS. Although NRS is considered to be a subjective index, it is widely used for its simplicity. In pain measurement, patients are asked to rate their pain by selecting a number from 0 to 10 that best represents their current pain severity (0 is “no pain”, and 10, “worst pain possible”) [20, 21].

Functional impairment will be evaluated using the accredited Korean version of the Oswestry Disability Index (ODI) [22]. The ODI is a 10-item questionnaire developed to assess level of disability due to LBP [23]. Each item is graded into 6 levels, each representing a score of 0–5. Higher scores indicate greater limitation relating to LBP.

For a more comprehensive evaluation of improvement in pain and functional disability, patient global impression of change (PGIC) will be assessed [20, 24]. PGIC grades the level of subjective improvement into 7 levels (1, very much improved; 2, much improved; 3, slightly improved; 4, no change; 5, slightly worse; 6, much worse; and 7, very much worse).

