### Sample size

There are no prior RCTs which have assessed the effect of *Shinbaro* pharmacopuncture in sciatic pain patients due to LDH. Therefore, the purpose of this pilot study is to calculate the sample size and assess the feasibility of a larger trial. A total of 60 participants with 20 patients per group will be recruited in light of the relatively short treatment and follow-up period. Factoring in a 20 % drop-out rate, we anticipate that this will be the minimum recommended number required for a pilot study [34].

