### Statistical analysis

The intention-to-treat and per-protocol analysis will be performed in all participants who complete the clinical trial with no major breach from the study protocol, and intention-to-treat will be the primary analysis. Missing values will be resolved using the last observation carried forward. Sociodemographic characteristics and treatment expectancy of study participants will be assessed by group. Continuous data will be presented as means and standard deviations, or medians and quartiles. One-way analysis of variance will be used if normally distributed, and Kruskal-Wallis test if not, and post-hoc analysis will be performed if there is a significant between-group difference. Categorical data will be expressed as frequencies and percents using chi-square test or Fisher’s exact test.

Analysis of covariance will be used to evaluate the primary outcome variable, VAS of sciatic pain at 5 weeks after randomization. Secondary outcome variables – VAS of LBP, NRS of sciatic pain, NRS of LBP, ODI, EQ-5D, and SF-36 -– will be assessed likewise. Between-group differences in PGIC and blinding assessment will use chi-squared tests.

Also, within-group differences before and after treatment (baseline and follow-up evaluations) will be examined using a paired *t* test or Wilcoxon signed rank test, and difference in time-by-treatment interactions using repeated measures analysis of variance. As an additional approach to quantify the difference among groups over total follow-up time, areas under the curve between the time of randomization and week 12 will be calculated and compared with 1-way analysis of variance.

All analyses will be performed using SAS version 9.1.3 statistical package (SAS Institute, Cary, NC, USA) with level of significance set at *p* < 0.05.

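### A chi-squared test for the seven-level PGIC ignores its ordering and wastes power at 20 per arm, and a non-significant chi-squared test would not show that blinding worked

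*Protocol article*

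**What the plan says.** All references are to the protocol article.

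- **Scale** (Secondary outcome measurements): "PGIC grades the level of subjective improvement into 7 levels". The levels run in order from very much improved (1) to very much worse (7). Table 1 schedules PGIC at weeks 5, 7 and 12.
- **Test** (Statistical analysis): "Between-group differences in PGIC and blinding assessment will use chi-squared tests".
- **General rule for categorical data** (same section): "Categorical data will be expressed as frequencies and percents using chi-square test or Fisher’s exact test".
- **Rank test already in the plan**, for continuous data: "One-way analysis of variance will be used if normally distributed, and Kruskal-Wallis test if not".
- **Size** (Sample size): "A total of 60 participants with 20 patients per group will be recruited", with this on attrition: "Factoring in a 20 % drop-out rate, we anticipate that this will be the minimum recommended number required for a pilot study".
- **Purpose of the blinding test** (Blinding): to judge whether masking succeeded among patients in the two acupuncture groups and for the initial acupuncture physician.

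The article mentions no collapsing of PGIC levels, no trend or ordinal method, and no criterion for successful blinding.

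**The concern.** The method for PGIC is stated, so this is a choice to examine and not a detail left to a later document. Pearson's statistic is unchanged if the seven levels are relabelled in any order. It therefore spreads its sensitivity over every kind of difference between arms, when the only one of interest is a shift towards improvement. With 20 per arm the table is also thin. At stake is a needless loss of information on a named secondary outcome.

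The blinding check has a different problem. A chi-squared test asks whether guesses differ between arms, and failing to find a difference in about 40 patients says little. This matters because the Discussion relies on masking an injection against a needle to separate the specific effect of pharmacopuncture from needling and placebo effects, and because the pilot is meant to inform a larger trial.

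**Working it through.** **Inputs.** From the document: 3 arms, 20 per arm, 7 levels, 20% drop-out (20 × 0.8 = 16 per arm, an inference) and significance at 0.05. The arm size is consistent with the total, 3 × 20 = 60. No power, effect size or PGIC distribution is stated, so there is no planned power figure to reproduce.

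**Step 1: table and sparse cells.** This assumes the uncollapsed table.
- Degrees of freedom: (3 − 1) × (7 − 1) = 12.
- Mean expected count: 60/21 = 2.9 per cell, or 48/21 = 2.3 at 16 per arm.
- With equal arms, an expected count of 5 needs 15 answers at that level across the three arms. Four such levels would use 4 × 15 = 60 answers and leave none for the other three. If all seven levels occur, at most three reach 5, so at least 4 of 7 (57%) fall below it. At 16 per arm, 48/15 = 3.2, so again at most three.

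**Step 2: power, by simulation.** Pearson chi-squared (empty levels dropped) was compared with Kruskal-Wallis (tie-corrected) under proportional-odds shifts. An example assumed control distribution over levels 1 to 7 is 5/20/35/25/8/5/2%. Its expected counts in an arm of 20 are 1, 4, 7, 5, 1.6, 1 and 0.4, so five of seven are below 5. The three arms are graded, with the middle arm about halfway on the log-odds scale (for example odds ratios 1, 2, 4).

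| Largest odds ratio, 20 per arm | Chi-squared | Kruskal-Wallis |
|---|---|---|
| 3 | 14% | 38% |
| 4 | 22% | 55% |
| 6 | 41% | 78% |
| 10 | 67% | 94% |

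At 16 per arm and odds ratio 4, the figures are 16% and 45%.

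Three seven-level distributions (the one above, one mostly improved, one uniform) and one using only four levels were run in two- and three-arm layouts at 20 per arm. The loss is 1 minus the share of rank-test power that chi-squared keeps.

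| Odds ratio | Loss, seven levels | Loss, four levels |
|---|---|---|
| 2 | 54–69% | 38–44% |
| 3 | 50–62% | 36–41% |
| 4 | 44–60% | 32–37% |
| 6 | 30–48% | 20–28% |
| 10 | 12–30% | 7–14% |

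The rank test was more powerful in every scenario with an effect. With no effect, chi-squared rejected 2.5–3.7% of the time where some levels are rare and up to about 5% otherwise; Kruskal-Wallis rejected 4.2–5.4%.

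**Step 3: blinding, 20 against 20.** Take a two-option guess and the uncorrected test. If 13/20 and 7/20 guess pharmacopuncture:
- χ² = 40 × (13 × 13 − 7 × 7)² / (20 × 20 × 20 × 20) = 3.6, so p = 0.058.
- The difference is 30 points. Its 95% half-width is 1.96 × √[(0.65 × 0.35 + 0.35 × 0.65)/20] = 0.296, so the interval runs from about 0 to 60 points.

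Exact power is 22% for 60% against 40%, 45% for 65% against 35%, and 71% for 70% against 30%. When both arms are near 50%, the half-width is 1.96 × √(0.5/20) = 0.31.

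**The case against.** The other side has several fair points.

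- **The power loss depends on assumptions.** This stands. The document gives no PGIC distribution, and a reader might infer from the odds ratio 4 row that chi-squared always loses more than half the power. The tables show otherwise for large shifts and for answers confined to about four levels.
- **A rank test would also often miss a modest shift.** True: 55% power at 20 per arm and 45% at 16 in the odds ratio 4 scenario. The pilot is not powered on PGIC, so the change makes better use of the data but does not make the comparison adequate.
- **Sparse cells do not inflate false positives here.** Also true. The simulated error rate is at or below 5%, so the harm is conservatism and lost power.
- **Fisher's exact test may be available.** The PGIC sentence can be read as shorthand within the general rule. That would answer the small-cell point, but Fisher's test also ignores the order.
- **Guess frequencies are already covered.** The general rule has categorical data shown as frequencies and percents. A reader might infer that the plan offers no per-arm estimate of guesses, or that it will declare masking successful on a non-significant p-value. The document supports neither. What remains is that the only inferential method named cannot establish success, and no interval is mentioned.

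**Conclusion.** The point holds for PGIC: the stated test discards the ordering of a seven-level scale and, if all levels occur, works on a table with at least 57% of expected counts below 5. Under the assumed distributions at 20 per arm, the loss relative to a rank test is roughly half or more for modest shifts over seven levels (odds ratios of 2 to 3, often 4). For larger shifts or about four levels in use it is mostly 15 to 45%, with extremes of 7% and 48%. These sizes rest on proportional-odds shifts and assumed control distributions. That the ordering is ignored does not.

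For blinding, the point is narrower. A non-significant chi-squared at 20 against 20 is compatible with a 30-point difference in guesses and must not be read as successful masking.

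The reach is limited. PGIC is a secondary outcome in a pilot, the primary VAS analysis is untouched, and no conclusion is biased towards a false positive.

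**What to change.** **PGIC.** Replace the chi-squared test with Kruskal-Wallis across the three arms and pairwise Wilcoxon rank-sum tests. Alternatively, fit a proportional-odds model and report odds ratios with 95% confidence intervals, which would also serve the planning of the larger trial. Keep the table of frequencies and percents.

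**Blinding.** State that a non-significant test will not be taken as evidence of masking. Alongside the planned frequencies and percents, report the proportion in each arm guessing each treatment with a 95% confidence interval, separately for patients and for the initial physician. A blinding index with its interval would also do, chosen to suit the response options on the form. The article does not list those options, so it should not be assumed that a don't-know answer exists.

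**Cost.** Analysis wording only. PGIC and the blinding test are already scheduled in Table 1, so no visit, form or sample size changes.

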### Randomization and allocation concealment

Random numbers will be generated by a statistician unaware of the design and purpose of this study through stratified block randomization in random blocks of 3 (1:1:1) using a computerized random number generator to allocate patients into 3 groups. SAS version 9.1.3 statistical package (SAS Institute, Cary, NC, USA) will be used. The random numbers will be stored in sealed envelopes until an investigator opens each envelope for random allocation. In situations where code break is warranted during the study, such as serious adverse events (SAEs), the principle investigator will contact the other researchers. Randomization will be performed only after the patient has been confirmed to be eligible, received LDH diagnosis through both clinical signs and radiologic evidence, and given written consent for participation. The patients will receive explanations about the two types of acupuncture (*Shinbaro* pharmacopuncture and acupuncture) which will be conducted by KMDs in accordance with recommendations for pharmacopuncture in the “Korean Medicine Clinical Practice Guideline for Lumbar Herniated Intervertebral Disc in Adults” [17]. They will also be informed of the contents of usual care, which will consist of individually tailored physical therapy and conventional medicine from commonly used treatments for LDH in accordance with Korean Health Insurance Review and Assessment Service data. The envelopes will be opened in view of the patient, and to prohibit reuse of envelopes, the patient name and date of opening will be recorded on each envelope and stored in a double-lock cabinet for the entire duration of the trial under the care of a custodian not involved in the study.

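### The supportive AUC comparison to week 12 uses one-way ANOVA with no baseline term: a valid test that gives up precision and protection against chance baseline imbalance

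*Protocol article*

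**What the plan says.** The Statistical analysis section of the protocol article sets two kinds of model for the outcome scores.

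- Primary outcome: "Analysis of covariance will be used to evaluate the primary outcome variable, VAS of sciatic pain at 5 weeks after randomization". The VAS of low back pain, both NRS scores, ODI, EQ-5D and SF-36 "will be assessed likewise". No covariates are listed.
- AUC: introduced with "As an additional approach to quantify the difference among groups over total follow-up time", after which "areas under the curve between the time of randomization and week 12 will be calculated and compared with 1-way analysis of variance". No covariate and no baseline-corrected form of the AUC is mentioned. The scale or scales to be summarised are not named.

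Table 1 places the VAS and ODI at visit 2, which is also the randomisation visit, and then at weeks 2, 3, 4, 5, 7, 9 and 12. The NRS is taken at screening and at every visit. A score from the day of randomisation therefore exists for each of these scales.

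The Sample size section states: "A total of 60 participants with 20 patients per group will be recruited". It gives no effect size, SD or power. Allocation is by "stratified block randomization in random blocks of 3 (1:1:1"), with no stratification factor named.

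**The concern.** An AUC that starts at randomisation includes a score on which treatment has had no effect. Its direct share of the area is small. The larger effect is indirect: patients who start with more pain tend to report more pain later, so the baseline score predicts the rest of the curve. A one-way ANOVA leaves that predictable variation in the error term. It also lets a chance difference between arms at baseline pass into the AUC difference. An analysis of covariance removes most of both, and the article already uses that kind of model for its other continuous outcomes.

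The stake is modest. No stated decision rests on the AUC test. The AUC is, however, the analysis meant to summarise the whole follow-up, and the pilot is meant to inform the size of a larger trial. A noisier contrast that moves with baseline imbalance is a weaker planning input than the same data could give.

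**Working it through.** **The plan's own figures.** The only arithmetic to reproduce is 3 × 20 = 60, and 20 × (1 − 0.20) = 16 completers per arm. There is no power calculation for the AUC.

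**Inputs.** From the documents: 20 per arm, three arms, the Table 1 VAS schedule, a 0–100 mm scale, and entry at NRS 5 or higher. Assumed, because the article gives none of them: the correlations between visits, the baseline SD, a significance level of 0.05 taken as two-sided, and that the visit-2 score is taken before the first treatment.

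**Step 1: weight of baseline in the AUC.** Counting from visit 2, the VAS times are 0, 1, 2, 3, 4, 6, 8 and 11 weeks. The trapezoid weights are 0.5, 1, 1, 1, 1.5, 2, 2.5 and 1.5. They sum to 11, and their squares sum to 18. Baseline carries 0.5/11 = 4.5%. If randomisation is instead set at week 0 with later readings at 1, 2, 3, 5, 7, 9 and 12, the share is 4.2% and the results below hardly change.

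**Step 2: correlation of baseline with the AUC.** Let b be the correlation of baseline with each follow-up score and f the correlation between follow-up scores, with unit variances. For the time-averaged AUC:

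- covariance with baseline: c = 0.0455 + 0.9545 b
- variance v = the sum of products of the weights with their correlations
- r = c/√v

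Under equal correlation b = f, v = f + (1 − f) × 18/121. For b = f = 0.3, c = 0.332, v = 0.404 and r = 0.332/0.636 = 0.52. For b = f = 0.5, c = 0.523, v = 0.574 and r = 0.523/0.758 = 0.69.

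**Step 3: variance reduction.** Adjustment multiplies the variance of an arm difference by 1 − r². Estimating the slope adds a factor of 1 + 1/(60 − 5) = 1.018. The effective number is 60/(1 − r²).

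| b | f | r | Cut, 1 − r² only | Cut with slope factor | Effective patients |
|---|---|---|---|---|---|
| 0.2 | 0.7 | 0.28 | 8% | 6% | 65 |
| 0.3 | 0.7 | 0.39 | 16% | 14% | 71 |
| 0.5 | 0.7 | 0.61 | 38% | 36% | 96 |
| 0.3 | 0.3 | 0.52 | 27% | 26% | 82 |
| 0.5 | 0.5 | 0.69 | 48% | 47% | 114 |

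In power terms, at f = 0.7, a pairwise effect with 80% power under ANCOVA has about 74% (b = 0.3) or 61% (b = 0.5) under the planned test.

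**Step 4: chance imbalance.** The SE of a pairwise baseline difference is SD × √(2/20). For SD 10, 15 and 20 mm it is 3.2, 4.7 and 6.3 mm. The normal probability of a gap above 5 mm is 0.11, 0.29 and 0.43. With no treatment effect, a 10 mm gap shifts the time-averaged AUC difference by an expected 10c: 3.3 mm at b = 0.3 and 5.2 mm at b = 0.5.

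**Step 5: validity.** In 20,000 simulated null trials with 20 per arm, b = 0.5 and f = 0.7, type I error was 0.049 unadjusted and 0.053 adjusted. Both estimates centred on zero, and the variance ratio was 0.65 (formula 0.64). Conditional on a baseline imbalance of 2 SE, the unadjusted pairwise error rate is about 0.10 (b = 0.3) to 0.18 (b = 0.5).

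**The case against.** The strongest reply is that nothing here is an error. One-way ANOVA on a randomised outcome is valid, and its standard error already allows for chance imbalance. The article labels the AUC as additional, and the primary and listed secondary scores have ANCOVA. This stands, and it limits the point to efficiency and conditional balance.

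The second reply concerns size, and it also stands. Equal correlation between all visits makes baseline as predictive as any later score. Restricted entry and four weeks of treatment argue for a weaker link, and then the gain may be only 8–16%. The baseline SD is also limited by the entry rule. If the VAS tracked the NRS, scores would lie between about 50 and 100 mm. The largest possible SD on that interval is 25 mm and a uniform spread gives 50/√12 = 14.4 mm, so 10–20 mm is the fairer range. Across it, a pairwise gap above 5 mm is plausible but less likely than not.

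A reader might go further than the article allows in three ways.

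- One might infer that the AUC result is biased or its overall type I error inflated. The simulation shows neither.
- One might attribute any disagreement between the AUC and week-5 results to baseline imbalance. Imbalance can contribute, but the two analyses estimate different quantities. The AUC also spans the post-treatment phase, in which the article allows pain medication as needed.
- One might say that the plan drops an adjustment it makes elsewhere. The article lists no ANCOVA covariates, so baseline as the covariate there is a natural inference, not a stated fact.

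What the reply does not remove is that the article names a specific test for the AUC when a more precise one needs only data already scheduled.

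**Conclusion.** The point holds as a minor improvement to a supportive analysis. The planned AUC comparison is valid but leaves out a baseline score that is collected, forms part of the AUC and is likely to predict the rest of it. The cost is a variance larger than necessary and exposure to chance imbalance in small arms.

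The reduction available ranges from about 8% at the weak end of the correlations considered to 48% at the favourable end. The 82–114 effective patients belong to the equal-correlation case and should not be read as the expected gain. All these figures rest on assumed correlations, and the imbalance probabilities rest on an assumed SD of 10–20 mm. The direction does not: unless baseline is almost unrelated to the AUC, adjustment gains precision. The primary week-5 analysis is not affected.

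**What to change.** Replace the one-way ANOVA for the AUC with an analysis of covariance that has arm as the factor and, as covariate, the score on the same scale at the randomisation visit, taken before treatment. Report the pairwise arm differences with 95% confidence intervals. In the same sentence, name the scale or scales for which the AUC is calculated.

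Taking the AUC of change from baseline would not replace the covariate. With follow-up correlation 0.7 and baseline correlation 0.3–0.5, that quantity correlates about −0.65 to −0.58 with baseline, so the dependence remains with the sign reversed.

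The cost is one phrase in the analysis plan and one residual degree of freedom (57 to 56 with all 60 patients). No new data or visits are needed.

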### Adverse events

Physicians will record all unexpected or unintended reactions at every patient visit in the *Shinbaro* pharmacopuncture, acupuncture, and usual care groups. The potential adverse effects of *Shinbaro* pharmacopuncture will include those known of acupuncture while keeping potential unknown adverse effects in mind. Physicians will rate the causal relationship of each treatment with the adverse event on a 6-point scale (1, definitely related; 2, probably related; 3, possibly related; 4, probably not related; 5, definitely not related; and 6, unknown), and classify all adverse events with the Spilker classification, which has 3 grades (1, mild: no intervention needed and does not greatly impede normal activity (function) of patient; 2, moderate: significantly impedes normal activity (function) of patient, and may need intervention, with subsequent resolution; 3, severe: severe adverse event needing intensive intervention, leaving sequela).

### Data handling and monitoring

Investigators will enter collected data into case report forms. Out-of-range or unclear entries and missing data will be recorded in data query forms, and sent to the investigational site for resolution. Data will be analyzed by baseline demographic characteristics, treatment effect, and safety assessment. Regular data monitoring will be conducted for quality control. Investigators will convene regularly to discuss any issues that may arise during trial operation, such as SAEs, protocol revision, and any important points raised by the investigators or participants.

### Safety monitoring

Safety assessments will focus primarily on frequency of adverse events including all SAEs. Adverse event information will be presented as number and percentage of participants who have experienced adverse events, and categorized by affected body region. Other collected information (e.g. severity, causal relationship) will be entered in safety monitoring reports.

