### Stopping rules

Due to lack of report on pharmacopuncture safety, researchers and clinicians convened for discussion and review of inhouse safety records of pharmacopuncture patients for the past 4 years and existing literature on acupuncture safety [35] to assess potential adverse events which may require the participant to be dropped out from the study. Symptoms requiring early withdrawal from the study included local infection, severe progressive neurological disorders, nerve irritation/injuries, continued bleeding in area administered with acupuncture, and pneumothorax. The trial will be stopped if the principle investigator judges that there is unacceptable risk of SAEs.

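### Adverse events are to be presented as participants by body region, with no commitment to show event type, severity or causality by arm

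*Protocol article*

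**What the plan says.** All references are to the protocol article.

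- **Safety monitoring** sets the focus: "Safety assessments will focus primarily on frequency of adverse events including all SAEs". It then fixes the presentation: "Adverse event information will be presented as number and percentage of participants who have experienced adverse events, and categorized by affected body region". The next sentence deals with the rest: "Other collected information (e.g. severity, causal relationship) will be entered in safety monitoring reports".
- **Adverse events** shows what is collected for each event. "Physicians will rate the causal relationship of each treatment with the adverse event on a 6-point scale", and they also "classify all adverse events with the Spilker classification, which has 3 grades". The top Spilker grade covers events that need intensive intervention and leave sequelae.
- **Stopping rules** names five kinds of event by type: "local infection, severe progressive neurological disorders, nerve irritation/injuries, continued bleeding in area administered with acupuncture, and pneumothorax". They are listed as grounds for early withdrawal, not as reporting categories.
- **Data handling and monitoring** adds in general terms: "Data will be analyzed by baseline demographic characteristics, treatment effect, and safety assessment".
- **Background** makes adverse events part of the comparison with usual care, and the Abstract and Discussion repeat safety as a purpose of the trial.
- **Interventions** places the second procedure, injection or needle, at the same marked paraspinal point to a depth of 4 cm in both needle arms.

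**The concern.** The article makes a presentation choice here, so the point does not rest on silence. Two adjacent sentences separate what is presented (participants with events, by region) from what is entered in monitoring reports (severity, causality).

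Taken as written, the presentation leaves out the information most useful for comparing harms:

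- A mild reaction and a grade 3 event with sequelae each count as one participant. So do an event rated definitely related and one rated definitely not related.
- The contrast between injection and needle is made at one shared anatomical point. Bruising, continued bleeding and local infection at that point can share a region, so region separates least where the injection's own effect is to be isolated.
- Against usual care, reactions to medication and needle-site reactions differ in kind and severity, and an ungraded percentage does not show this.

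At stake is how much a reader, or the team planning the larger trial, can learn about comparative safety. The primary analysis, the sample size and the error rates are not affected.

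**Working it through.** **1. What is collected against what the presentation uses.**

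| Item | Collected? | Used in the stated presentation? |
|---|---|---|
| Any event, per participant | Yes (Adverse events) | Yes |
| Body region | Implied (Safety monitoring) | Yes |
| Seriousness | Yes (SAEs named) | Within the frequency count; no separate tabulation stated |
| Severity, 3 grades | Yes, every event | Assigned to monitoring reports |
| Causality, 6 points | Yes, every event | Assigned to monitoring reports |
| Event type, as in Stopping rules | Yes, as withdrawal grounds | Not a stated category |

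The article gives no adverse event rate, power or margin, so there is no plan figure to reproduce. The only design figure used below is 20 participants per arm.

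**2. How far a participant count can blur a distinct harm.** This is an illustration. The rates are assumed, and so is the pooling of all events in one region.

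Let *b* be the proportion with a minor reaction in either needle arm, and *h* = 0.10 an independent added risk of a distinct harm with the injection. The proportion with any event in that region is then

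1 − (1 − *b*)(1 − *h*).

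| *b* | Injection arm | Needle arm | Extra participants of 20 | Harm shown by type |
|---|---|---|---|---|
| 0.10 | 1 − 0.90 × 0.90 = 19% | 10% | 1.8 | 2/20 v 0/20 |
| 0.30 | 1 − 0.70 × 0.90 = 37% | 30% | 1.4 | 2/20 v 0/20 |
| 0.50 | 1 − 0.50 × 0.90 = 55% | 50% | 1.0 | 2/20 v 0/20 |
| 0.70 | 1 − 0.30 × 0.90 = 73% | 70% | 0.6 | 2/20 v 0/20 |

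The blurring grows with the background rate: slight at 10%, and more than half of the two harm cases at 70%.

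If the any-event proportions were tested at two-sided 5% with 20 per arm (normal approximation, rejection in the direction of harm), power would be about 12%, 7% and 5% for *b* = 0.10, 0.30 and 0.50. For *h* from 0.05 to 0.15 over the same backgrounds it runs from about 4% to 20%. The article names no such test; these figures only show how little the any-event contrast carries.

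**3. What 20 per arm allows under any layout.**

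- With 0 events in 20, the one-sided 95% upper bound is 1 − 0.05^(1/20) = 13.9%. With 16 completers (20 less the 20% drop-out) it is 17.1%.
- The chance of at least one event in 20 is 1 − 0.95^20 = 64% at a true rate of 5%, and 1 − 0.99^20 = 18% at 1%.
- Even 2/20 against 0/20 gives a two-sided Fisher p of about 0.49.

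A better table therefore improves the description and does not make the trial able to test for harms.

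**The case against.** The strongest reply is that the presentation is not exclusive and that this is a condensed article about a pilot. Much of that stands, and it rules out several stronger readings.

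- **That body-region counts are all that will be reported.** A reader might infer this, but nothing in the text says so. SAEs are expressly included, and entering ratings in monitoring reports does not bar them from the results. The supportable statement is that there is no commitment to show them.
- **That the important harms would be concealed.** The Stopping rules state: "Symptoms requiring early withdrawal from the study included local infection, severe progressive neurological disorders, nerve irritation/injuries" and others, so such events should be identifiable as withdrawals, and the serious ones as SAEs. No region scheme is given. Pneumothorax would not fall in the low back, and nerve irritation may be located in the leg.
- **That the repeat blood tests will go unanalysed.** Table 1 schedules them at screening, week 5 and week 12, and the article describes no analysis. An article commonly leaves that detail to the full protocol or analysis plan, so it is no finding.
- **That only animal data support the solution.** The Stopping rules section cites four years of in-house safety records, and the Discussion reports 104,445 outpatients given this preparation. The same Stopping rules section does acknowledge a lack of safety reports.
- **That minor reactions will be common in both needle arms.** In the acupuncture arm the soreness is produced on purpose. The Adverse events section records reactions that were not expected or not intended, so this soreness may not be counted. The background rate is unknown and could be low.

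The reply does not remove the central point. The article itself chose region as the category and placed the ratings elsewhere, although comparative safety is an aim and every event is already graded.

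**Conclusion.** The point holds as a low-severity weakness in a stated presentation choice. The Safety monitoring section commits to participant counts by body region and makes no commitment to show event type, severity or causality by arm.

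Its size cannot be fixed from the document, because no event rates are given. Under the assumed rates, a harm affecting 2 of 20 appears as 0.6 to 1.8 extra participants in the region line. That range rests on independence, on an added harm of 10% and on all events falling in one region. If background reactions are rare, or the harms fall in different regions, the loss is smaller.

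No estimate is biased and no sample size, significance level or primary analysis changes. Safety results stay descriptive at 20 per arm.

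**What to change.** Amend the Safety monitoring section so that adverse events are tabulated:

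- by randomised arm and event type, with the events listed under Stopping rules as named categories and a category for all others;
- by seriousness, Spilker severity grade and the 6-point causality rating, also by arm;
- as both participants and events, with body region kept as a descriptive column.

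State that these tables are descriptive.

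The cost is a change of wording and a few more tables from data already collected. It needs no extra participants, visits or tests, and it leaves every clinical and withdrawal rule as it is.
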